Participants assigned to the control group will receive standard educational care regarding their illness and in-person check-ups based on the study’s outcome schedule and the determination of their attending physician. However, once the study’s follow-up period is completed, participants assigned to the control group will be offered access to this application. 

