*Contigo* comprises six modules: El Viaje (Spanish for The Journey, care process information), Mis Resultados (My Results, self-perception of health reporting), Mis Experiencias (My Experiences, reporting experiences during healthcare and cancer treatment), Asistencia (Assistance, frequently asked questions), Comunidad (Community, complementary non-clinical information), and Programación (Scheduling, medical appointment and procedure requests). Users have continuous access to these modules, and questionnaires are displayed according to the clinical trial schedule. The source code will not be published, but a website (https://infanticontigo.cl/, accessed on 3 December 2023) will provide information about the application and a functional demo version for potential users. Patients participating in the clinical trial will receive the application at no cost, with usernames and passwords provided during training by the monitoring nurse. The research team will offer technical support, while clinical assistance will be provided by healthcare professionals. A depiction of the user interface of *Contigo* is depicted in Figure 2.

*Contigo* is founded upon a robust security infrastructure designed to safeguard the integrity and confidentiality of data. HTTPS is employed to ensure the secure transmission of information between the client and the server. Passwords are stored in encrypted form, and hash techniques are applied to protect sensitive database data. Environment variables and system keys are generated during the execution of the deployment pipeline, preventing their inclusion in configuration files or source code, and ensuring they remain unknown to developers. Through these measures, a secure environment is maintained to preserve the privacy of users and the integrity of stored information.

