The participants’ health-related quality of life will also be assessed using the EuroQol Group’s EQ-5D questionnaire. This tool evaluates an individual’s perception of their health status based on well-being in five dimensions: mobility, self-care, usual activities, pain/discomfort, and anxiety/depression. Each of these dimensions is subdivided into five response levels for each question, and scores can be assigned to synthesize an individual’s quality of life. In addition to the questions for each dimension, the EQ-5D questionnaire includes a synthesis measurement represented by a visual analog scale regarding the individual’s self-perceived current health state. The scale is a 20 cm line graduated in units where the top end represents 100 points denoting the “best imaginable health state”, and the bottom end represents 0 points indicating the “worst imaginable health state”. The respondent evaluates their current health state by drawing a line from the box marked “your own health state today” to the point that best represents their health on this visual analog scale. This questionnaire was chosen for its validation for use among oncology patients [28], as well as its favorable psychometric properties and ease of use, enabling self-administration, validation in multiple languages including Spanish, and application among Chilean patients [29,30]. All these baseline measurements will be performed once during the initial study visit by the research team, taking the form of an initial clinical interview.

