### 3.5. Outcomes

The primary outcome of this study is the change in quality of life quantified using the EQ-5D questionnaire measured at 30, 60, and 90 days after randomization. The five-level version of the questionnaire will be used (EQ-5D-5L). Additionally, the measurement of quality of life specific to the 3 domains established by the previous questionnaire has been established as co-primary outcomes. The questionnaire will be electronically delivered through the mobile application or via emails for participants to self-administer, considering its psychometric properties, when reaching the aforementioned follow-up milestones of the study. If electronic delivery of the questionnaire is not possible, it can be completed during in-person visits of the study participants.

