As a secondary outcome, the difference in the development of depressive symptoms during the follow-up has been established. These symptoms will be evaluated based on the Patient Health Questionnaire 9 (PHQ-9) scale [31]. This diagnostic tool consists of 9 questions assessing the level of depression in an individual. The first 8 questions accumulate a score ranging from 0 to 3 points, where higher scores suggest a higher probability of depression. The ninth question is used to determine the impact of the patient’s symptoms on their personal life. Scores equal to or greater than 10 points demonstrate good diagnostic performance, with a sensitivity of 88% (95% Confidence Interval, CI 95% 83–92%) and specificity of 85% (CI 95% 82–88%) based on a recent systematic review [32]. This scale was chosen not only for its clinical performance but also for its extensive use in various clinical settings [31,33,34] and spectrums of chronic comorbidities [35,36]. It is important to note that the questionnaire is validated for use in the Spanish language and in the Chilean population [37]. Additionally, this tool is designed to be applied without the need for a healthcare provider’s intervention [38,39], thus it can be virtually implemented through the same application within the same time frames as the EQ-5D tool. In case of a positive screening for depression using the aforementioned scale, the treating team will be notified of the result for confirmation and treatment inclusion in participant management. Also, adherence to medical appointments established by the treating team will be evaluated as a secondary outcome, defined as the proportion of in-person attendance at medical and nursing appointments during the study period.

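### The route by which EQ-5D-5L and PHQ-9 are collected is tied to the arm: the app is one named route for the first and the only named route for the second, and controls have no app during follow-up

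*Protocol article*

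**What the plan says.** All places are in the protocol article.

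- **EQ-5D-5L, the primary outcome at days 30, 60 and 90 (section 3.5).** "The questionnaire will be electronically delivered through the mobile application or via emails for participants to self-administer". The fallback is also stated: "If electronic delivery of the questionnaire is not possible, it can be completed during in-person visits of the study participants".
- **PHQ-9, a secondary outcome (section 3.5).** After noting that the scale needs no health professional to administer it, the text concludes "thus it can be virtually implemented through the same application within the same time frames as the EQ-5D tool". It does not mention email or an in-person fallback for PHQ-9.
- **Questionnaires in the app (section 3.3).** Users can open the modules at any time, and "questionnaires are displayed according to the clinical trial schedule".
- **Controls (section 3.2).** They do not have the app during the trial: "once the study’s follow-up period is completed, participants assigned to the control group will be offered access to this application". Until then they receive standard education and "in-person check-ups based on the study’s outcome schedule and the determination of their attending physician".

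The article nowhere requires the two arms to answer by the same route.

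**The concern.** EQ-5D-5L and PHQ-9 are self-reports, and a patient cannot be unaware of having been given an app. With such outcomes, the circumstances of answering should be the same in both arms. Here one arm can answer inside the product under test and the other cannot.

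Two things could then differ between the arms for reasons unrelated to quality of life or mood. One is who answers: completion may be higher where the form appears in software that the patient already uses and was trained on. The other is how they answer: the same patient may respond differently in an app, on an emailed form, or at a visit. The blinded statistician of section 3.6.2 protects against neither, and the questionnaire validation cited in section 5 does not make the routes interchangeable between arms.

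PHQ-9 is the sharper case, because the only route named is one that controls lack. Section 3.5 also has positive screens passed on to the treating team, so unequal collection could lead to unequal detection of depression.

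**Working it through.** **Step 1. The routes side by side, days 30 to 90**

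| Questionnaire | App arm | Control arm |
|---|---|---|
| EQ-5D-5L | app, email, or in person as fallback | email, or in person as fallback |
| PHQ-9 | app | none named |

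The app column follows from sections 3.3 and 3.5. The control column is the same list with the app struck out, as section 3.2 requires. How app-arm patients would divide between app and email is not stated. If all use the app, route and arm coincide completely. If some use email, the overlap is partial, but the choice of route within that arm is not randomised, so an analysis that adjusts for route would not restore a randomised comparison.

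**Step 2. How large could unequal completion be?**

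The article gives no completion rates and no mode effect, so these are assumptions: completion 95% in the app arm and 80% in controls; non-completers lower than completers by D on EQ-5D, with the same D in both arms; completers compared without correction.

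If a fraction m is missing, the full mean equals the completers' mean minus m × D, so the observed mean is too high by m × D. The bias in the difference (app minus control) is therefore −(0.20 − 0.05) × D = −0.15 × D.

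| D (assumed) | Control mean too high by | App mean too high by | Bias in difference | Share of the 0.1 target (section 3.6.1) |
|---|---|---|---|---|
| 0.10 | 0.020 | 0.005 | −0.015 | 15% |
| 0.20 | 0.040 | 0.010 | −0.030 | 30% |
| 0.35 | 0.070 | 0.0175 | −0.0525 | 53% |

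In this example the bias works against the app.

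**Step 3. What would a shift in answers due to route do?**

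Inputs from section 3.6.1: 40 per arm, SD 0.35, r = 0.7, three measurements, two-sided 5%. Assumed: no true effect, and a route-related shift b of 0.02 to 0.05 points (20% to 50% of the target) between the arms. SE = 0.35 × √factor × √(2/40), and the rejection rate is Φ(b/SE − 1.96) + Φ(−b/SE − 1.96).

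| Analysis | Variance factor | SE | b = 0.02 | b = 0.05 |
|---|---|---|---|---|
| Mean of three follow-ups | (1 + 2r)/3 = 0.80 | 0.070 | 5.9% | 11.0% |
| Change from baseline | 0.80 + 1 − 2r = 0.40 | 0.049 | 6.9% | 17.3% |
| Baseline-adjusted (ANCOVA) | 0.80 − r² = 0.31 | 0.044 | 7.4% | 20.9% |

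The nominal rate is 5%. The planning values serve only as a yardstick. Whether 80 patients follow from them is a separate question on which this point does not depend.

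**The case against.** The strongest reply is that the primary outcome is covered: controls have two stated EQ-5D-5L routes, and nothing forbids emailing app-arm patients as well. The PHQ-9 sentence is permissive, a remark on feasibility that excludes no other route. The article also condenses a fuller protocol, where delivery logistics and reminders would normally be found.

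Much of this stands. It would be wrong to say that the outcome questionnaires as a whole run through the app, or that PHQ-9 cannot be obtained from controls. What remains is that the article does name routes, that one of them is open to a single arm, and that no common route is required. Condensation does not explain that.

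A reader might infer more, without support in the text:

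- **That only controls have check-ups on the outcome schedule.** Section 3.2 states these for controls, but no passage rules them out for the app arm, whose visit schedule is not described.
- **That the app arm gets extra prompts.** Section 3.3 lists push notifications as a general feature of this type of app, not as outcome reminders.
- **That study visits inflate the adherence outcome.** Sections 2 and 3.5 tie adherence to appointments set by the treating team, which on its face leaves out visits made only for the study.
- **That the baseline interview adds to the difference.** Section 3.4 describes baseline collection as "taking the form of an initial clinical interview", but this applies to everyone, so it is not a difference between arms.

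**Conclusion.** The concern holds in this form: followed as written, the plan ties collection route to arm for self-reported primary and secondary outcomes in patients who know their allocation, and it names no PHQ-9 route for controls. Once the data are in, analysis cannot reliably separate a route effect from a treatment effect.

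The sign and size of the bias are unknown. The 0.015 to 0.053 points from unequal completion rest entirely on assumed rates and deficits. The rejection rates of about 6% to 21% rest on an assumed shift. A shift in answers due to route could add to a completion bias or offset it, so the two should not be summed. The illustrations show only that modest differences would matter against a 0.1-point target; they do not predict a bias.

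This does not invalidate the trial. It is an avoidable weakness that should be corrected because the remedy is cheap.

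**What to change.** 1. In section 3.5, deliver EQ-5D-5L and PHQ-9 at days 30, 60 and 90 to both arms by one identical channel outside the app. The emailed form already foreseen for EQ-5D-5L would serve. Use the same reminders and the same in-person fallback in both arms and for both questionnaires.
2. Do not show these two questionnaires again in the app at those time points, so that app-arm patients are not asked twice. Align the statement in section 3.3 on the display of questionnaires.
3. Reconcile sections 3.2 and 3.5: state how controls complete PHQ-9, and whether check-ups on the outcome schedule apply to both arms or to one.

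The cost is one web form and a few sentences of protocol wording. The small downside is that app-arm patients answer an emailed form at three time points instead of answering in the app.

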### 3.6. Statistical Analysis

#### 3.6.1. Sample Size

Current literature on the potential effect of telemonitoring platforms on outcomes such as quality of life is scarce. However, based on previous reports [40,41], it has been estimated that a total of 80 participants (40 per arm) will be necessary to achieve 80% statistical power at standard significance levels (5% alpha two-tailed), assuming an intergroup difference in EQ-5D questionnaire means of 0.1 point, a symmetric standard deviation between groups of 0.35 points, a strength of linear correlation between measurements of 0.7 (r = 0.7), and 3 instances of measurement for both groups.

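### The inputs in section 3.6.1 do not give 80% power with 40 per arm; they give about 52% for mean change from baseline and at best about 63%

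*Protocol article*

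**What the plan says.** Section 3.6.1 (Sample Size) states that "a total of 80 participants (40 per arm) will be necessary to achieve 80% statistical power at standard significance levels", with alpha given as "5% alpha two-tailed". It lists the inputs: "assuming an intergroup difference in EQ-5D questionnaire means of 0.1 point, a symmetric standard deviation between groups of 0.35 points", and "a strength of linear correlation between measurements of 0.7 (r = 0.7"), with three measurement occasions in both groups. The calculation is said to rest on earlier reports, but no formula or test is named.

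Other sections fix the measurement schedule. Section 3.4 (Variables) includes EQ-5D in the baseline profile and says: "All these baseline measurements will be performed once during the initial study visit by the research team". Section 3.5 (Outcomes) defines the primary outcome as change in EQ-5D, "measured at 30, 60, and 90 days after randomization". The design therefore has one baseline and three follow-up measurements.

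Section 3.6.2 (Analysis Strategy) plans a repeated-measures ANOVA of the change in EQ-5D. Regression adjustment is foreseen only if participant characteristics turn out to be imbalanced.

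**The concern.** The listed inputs are complete enough to recalculate the power, and the stated figure does not follow from them. A difference of 0.1 against an SD of 0.35 is a standardised difference of 0.286. At one visit, 80% power for that needs about 193 per arm. Repeated measurement lowers the requirement, but with r = 0.7 and one baseline it does not come down to 40.

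This is the only justification given for the size of the trial on its primary outcome. If the 80% stands, a null result is likely to be read as good evidence against a 0.1 effect. On the stated inputs, an analysis of mean change would miss a true 0.1 effect about 48% of the time, not 20%. Section 5 mentions sample size as a limitation but does not correct the figure.

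**Working it through.** **Inputs.** From 3.6.1: difference d = 0.1, SD = 0.35 in each group, r = 0.7, two-sided alpha 5%, power 80%, 40 per arm. From 3.4 and 3.5: one baseline and three follow-ups. Assumptions: r = 0.7 applies to every pair of measurements, because only one value is given, and there is no loss to follow-up.

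**Formulas.** With variance factor f for the summary measure:

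- n per arm = 2 × (1.960 + 0.842)² × 0.35² × f / 0.1² = 192.3 × f
- standard error at 40 per arm = 0.35 × √f × √(2/40)
- power = Φ(0.1/SE − 1.960)
- difference detectable with 80% power = 2.802 × SE

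**Variance factors for one baseline and three follow-ups.**

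- Mean of follow-ups, baseline not used: f = (1 + 2 × 0.7)/3 = 0.80
- Mean change from baseline: f = 0.80 + 1 − 2 × 0.7 = 0.40
- Mean of follow-ups adjusted for baseline: f = 0.80 − 0.7² = 0.31

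| Analysis | f | SE at 40 per arm | Power for 0.1 | n per arm for 80% | Detectable with 80% |
|---|---|---|---|---|---|
| Mean of follow-ups | 0.80 | 0.0700 | 29.8% | 154 | 0.196 |
| Mean change | 0.40 | 0.0495 | 52.4% | 77 | 0.139 |
| Baseline-adjusted | 0.31 | 0.0436 | 63.1% | 60 | 0.122 |

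With the t distribution in place of the normal, the powers are 29.2%, 51.4% and 62.0%.

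**As repeated-measures ANOVA F tests.**

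- Between-group test on the three follow-ups: noncentrality 20 × 0.1² × 3 / (0.35² × 2.4) = 2.04 on 1 and 78 df, power 29.2%.
- Group-by-time test over four occasions with differences 0, 0.1, 0.1, 0.1: the squared deviations from their mean of 0.075 sum to 0.0075, so the noncentrality is 20 × 0.0075 / (0.35² × 0.3) = 4.08 on 3 and 234 df, power 36.0%.

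**Other readings.**

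- Three occasions taken as one baseline plus two follow-ups: 28%, 48% and 57% in the order of the table.
- A one-sided 5% test, which the text rules out: 41%, 65% and 74%.
- What 40 per arm would require: f = 40/192.3 = 0.208. For mean change, f = (4/3)(1 − r), so r = 1 − 0.75 × 0.208 = 0.844. With baseline adjustment, r must be about 0.82. If r stays at 0.7, the SD would have to be about 0.25 (change) or 0.29 (adjusted) instead of 0.35.

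**Attempts to reproduce the 80.** Two routes come close, and both depart from the stated design or inputs.

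- Entering 0.1/0.35 = 0.286 as Cohen's f in the between-group repeated-measures test, with three measurements and r = 0.7: noncentrality 0.286² × 80 × 3 / 2.4 = 8.16, power 80.6% at a total of 80 and 79.5% at 78. This gives exactly 80. For two equal groups, however, Cohen's f is half the standardised difference, 0.143, and the power is then 29.2%.
- Three baselines and three follow-ups analysed as change: f = 0.80 + 0.80 − 1.4 = 0.20, or 39 per arm and 78 in total. Section 3.4 provides for a single baseline measurement.

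**The case against.** **The exact powers depend on assumptions.** Section 3.6.1 gives one correlation without saying which pairs it covers, and does not say which ANOVA test was powered. This is fair, and each percentage above is conditional on equal correlation. It does not rescue the 80%, since no variant that respects the stated inputs and the single baseline reaches it.

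**30% is a poor headline for an outcome defined as change.** This also stands. The 30% figure leaves the baseline out. For sections 3.5 and 3.6.2 as written, mean change (52%) or group-by-time (36%) is closer.

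**63% belongs to an analysis the article does not plan as primary.** Correct. It marks the most favourable case and cannot replace the 80% unless 3.6.2 changes too.

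Two stronger readings are tempting but unsupported:

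- A reader might infer that the planners entered three baselines by mistake, in conflict with section 3.4. The Cohen's f route gives 80 exactly and needs no extra baselines. The article documents neither route, so the origin remains unknown.
- A reader might count the absence of a dropout allowance as a further error. A condensed article may leave this to the full protocol, so the point does not rest on it.

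**Conclusion.** The concern holds. The statement that 40 per arm gives 80% power for a 0.1 difference is wrong on the article's own inputs. With r = 0.7 between all pairs, one baseline, three follow-ups and no loss, the power is about 52% for mean change, about 36% for a group-by-time test with a constant 0.1 difference after baseline, about 29% to 30% for the follow-ups alone, and at best about 63% with baseline adjustment. The differences detectable with 80% power are 0.14 for mean change and 0.12 with baseline adjustment, both above the planned 0.1.

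The mismatch is one of stated power. It does not make the trial's comparison invalid, and it does not by itself require more participants.

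**What to change.** Keep 80 participants and restate the power in 3.6.1 for the analysis in 3.6.2. Possible wording: With 40 participants per arm, SD 0.35, a correlation of 0.7 between all pairs of measurements, one baseline and three follow-ups, the comparison of mean change in EQ-5D from baseline has about 52% power for a difference of 0.1 and 80% power for 0.14 (two-sided 5%). Section 3.6.2 should say that this between-group comparison of mean change is the primary test, since a group-by-time test would have different power.

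Alternatively, make the baseline-adjusted comparison of mean follow-up EQ-5D the primary analysis in 3.6.2, and state about 63% power for 0.1 and 80% for 0.12. This is the more efficient choice, but it changes the analysis plan as well as the sample-size text.

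In either case, name the formula, state the equal-correlation assumption, and give the numbers of baseline and follow-up measurements separately. If the 80 rested on an assumption that the article does not show, disclose it. The cost is a change of wording in 3.6.1, plus 3.6.2 where noted, and a less favourable power statement. No further recruitment is needed to make the statement true.

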#### 3.6.2. Analysis Strategy

For the statistical analysis, means, medians, standard deviations, interquartile ranges, ranges, and absolute and relative frequencies will be used for descriptive analysis. Inferential analysis will employ Student’s *t*-test or the Mann–Whitney U test for comparing means based on data distribution and variances, and Fisher’s Exact Test for evaluating categorical variables. The primary outcome will be evaluated in relation to the change in EQ-5D score means associated with their corresponding standard deviations through a repeated measures analysis of variance (ANOVA). Confidence intervals at 95% will also be constructed from the standard deviations of the mean changes to estimate the magnitude of the intervention effect among these patients. Additionally, the potential association between the implemented intervention and the development of categorical outcomes will be quantified using the relative risk statistic associated with their corresponding 95% confidence intervals. Subgroup analysis has not been considered in this study.

If an imbalance in participant characteristics is detected, confounding will be controlled using multivariable linear regression analyses. Model assumptions will be assessed graphically and by an evaluation of residuals. Heteroskedasticity will be addressed using the Cook–Weisberg method. All analyses will be conducted by a statistician unaware of the participants’ treatment assignment, following the intention-to-treat principle, and using Stata v.16.0^®^ software (StataCorp LP, StataCorp LLC., College Station, TX, USA, 1996–2020).

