### 3.1. Participants

Eligible participants will be adult patients (≥18 years old) with a recent histologically confirmed diagnosis (within the last 3 months) of bronchogenic, breast, gallbladder, gastric, colorectal, or prostate cancer in any of its forms. These patients should be awaiting the initiation of curative intent treatment for the disease using any modality (radiation therapy, chemotherapy, immunotherapy, etc.) at the UC-Christus Cancer Center during the months of November 2023 to June 2024. It was decided not to include patients with hematological neoplasms at this stage because most chemotherapy regimens provided for these forms of cancer are delivered within hospitals in Chile. Participants will be required to possess a smartphone, regardless of its native operating system (iOs^®^ or Android^®^). All selected patients will be required to sign an informed consent form to participate in this study. Individuals with any form of sensory impairment preventing app usage, cognitive impairment, psychiatric pathology hindering app usage, or those unwilling to participate in the study will be excluded. Patients concurrently participating in another clinical trial addressing healthcare technologies will be excluded as well. 

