### 3.4. Variables

For each patient enrolled in the study, a baseline clinical profile will be developed, including demographic, household characterization, clinical, and neoplasia-related information. Briefly, this profile will consist of demographic data, encompassing information about gender, age, highest level of education attained, marital status (single, married, cohabiting), healthcare system affiliation (Fondo Nacional de Salud, FONASA, public healthcare; Institución de Salud Previsional, ISAPRE, private insurance; or other); household characterization data including socioeconomic level, overcrowding, availability of basic services, migratory status, and support networks; and clinical information. The latter section will comprise data on relevant medical comorbidities (diabetes mellitus, heart failure, chronic obstructive pulmonary disease, bronchial asthma, chronic liver disease, fibromyalgia, coronary artery disease, and chronic kidney disease), concurrent psychiatric conditions (depression, anxiety disorders, personality disorders), habits (alcohol consumption, substance use, or smoking), and neoplasia-related information, including the specific cancer type, date of diagnosis, stage at diagnosis based on TNM (tumor, nodes, and metastasis) classification, and therapy received.

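### Covariate adjustment hangs on a detected chance imbalance, and the protocol does not say whether the adjusted or the unadjusted result is primary

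*Protocol article*

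**What the plan says.** Section 3.6.2 evaluates the change in mean EQ-5D score "through a repeated measures analysis of variance (ANOVA") and names no covariate. The next paragraph adds the adjustment rule: "If an imbalance in participant characteristics is detected, confounding will be controlled using multivariable linear regression analyses". It gives no test or threshold for imbalance, no list of candidate covariates and no order of precedence between the two analyses. It does say that a statistician who does not know the allocation will do all analyses.

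The candidate characteristics are in section 3.4:
- demographic: "gender, age, highest level of education attained, marital status (single, married, cohabiting), healthcare system affiliation"
- household: "socioeconomic level, overcrowding, availability of basic services, migratory status, and support networks"
- comorbidities: "diabetes mellitus, heart failure, chronic obstructive pulmonary disease, bronchial asthma, chronic liver disease, fibromyalgia, coronary artery disease, and chronic kidney disease"
- psychiatric conditions: "depression, anxiety disorders, personality disorders"
- three habits: alcohol, substance use and smoking
- neoplasia-related: cancer type, date of diagnosis, and "stage at diagnosis based on TNM (tumor, nodes, and metastasis) classification, and therapy received"

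The same section collects EQ-5D at baseline and places the baseline measurements at the initial study visit, taken once. Section 3.2 describes 1:1 allocation by permuted blocks with a concealed algorithm and names no stratification factor. On treatment status at entry, section 3.1 says: "These patients should be awaiting the initiation of curative intent treatment for the disease using any modality".

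**The concern.** Under concealed random allocation, a difference between arms in a baseline characteristic is a chance event. It says nothing about whether that characteristic predicts EQ-5D. A rule that adjusts for whatever differs therefore selects on luck. It will often add covariates that explain nothing and pass over prognostic ones that happen to look balanced, although adjusting for the latter is what reduces the standard error.

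The rule also leaves two candidate estimates, one from the ANOVA and one from the regression. Which of them is reported as the trial's answer, and with which covariates, would be settled after the data are seen. In a trial of 80 patients both the lost precision and the open choice matter.

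**Working it through.** **The plan's own figure.** The protocol gives no number for the imbalance rule. Its only design figure is 80 participants (40 per arm) for 80% power (section 3.6.1). One baseline and three follow-ups do not reproduce it: change scores need 77 per arm. Only three baselines with three follow-ups come close (39 per arm), and section 3.4 takes the baseline once. That is a separate matter. The power figures below serve only to compare two analyses at 40 per arm.

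**Step 1: count the characteristics in section 3.4.** 5 demographic + 5 household + 8 comorbidities + 3 psychiatric + 3 habits + 4 neoplasia-related = 28. Counting comorbidities, psychiatric conditions and habits as one item each gives 28 − 14 + 3 = 17.

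**Step 2: how often chance triggers adjustment.** Assume imbalance means p<0.05 and the items are independent. Then P(at least one flag) = 1 − 0.95^k.

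| k | P(at least one) |
|---|---|
| 10 (heavier grouping, illustrative) | 40% |
| 17 | 58% |
| 20 | 64% |
| 28 | 76% |

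With k = 28 the expected number of flags is 28 × 0.05 = 1.4. Section 3.6.2 assigns categorical variables to Fisher's exact test, which is conservative. At 40 per arm its actual size is about 0.4%, 1.7% and 2.8% for assumed prevalences of 5%, 10% and 20%. Applying these sizes to the 14 comorbidity, psychiatric and habit items, and 5% to the other 14:
- 1 − 0.95^14 × 0.996^14 = 54%
- 1 − 0.95^14 × 0.983^14 = 62%
- 1 − 0.95^14 × 0.972^14 = 67%

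**Step 3: what fixing baseline EQ-5D gains.** Inputs from section 3.6.1: difference 0.1, SD 0.35, r = 0.7, three follow-up measurements, two-sided 5%, 40 per arm. Assume the same correlation between all pairs of visits, including baseline, and an effect averaged over the three follow-ups.
- Variance factor of the follow-up mean: (1 + 2 × 0.7)/3 = 0.80
- Change from baseline: 0.80 + 1 − 2 × 0.7 = 0.40
- Baseline as covariate: 0.80 − 0.7² = 0.31

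Standard error = 0.35 × √factor × √(2/40); power ≈ Φ(0.1/SE − 1.96).
- Change: SE = 0.0495; 0.1/SE = 2.02; power about 52%
- Covariate: SE = 0.0436; 0.1/SE = 2.30; power about 63%

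For 80% power the requirements are 77 and 60 per arm.

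**Step 4: the rule against fixed covariates.** Simulation with 40 per arm, one outcome, and 28 independent normal covariates of which 4 are prognostic; selection at p<0.05; 6,000 runs per setting; assumed standardised effect 0.5.

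| | R² = 0.3 | R² = 0.5 |
|---|---|---|
| Power, unadjusted | 60% | 60% |
| Power, adjust if imbalanced | 57% | 57% |
| Power, 4 prognostic covariates fixed | 73% | 86% |
| Type I error, rule followed strictly | 4.6% | 3.6% |
| Type I error, better of adjusted and unadjusted | 6.7% | 6.0% |

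The rule selected at least one covariate in about 76% of runs, but a prognostic one in only about 19%.

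**The case against.** Several points on the other side have force.

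- **The criterion is not stated.** The protocol speaks only of detection and specifies no 5% test. Any trigger frequency is therefore conditional, and a range is more honest than the single figure of 76%. This stands.
- **Baseline is already used.** The primary outcome is a change score, so baseline EQ-5D is not ignored. That is right, and the gain in step 3 is measured against change scores for that reason.
- **The regression may be supplementary.** Naming the ANOVA for the primary outcome allows that reading. The text does not confirm it, and one sentence would settle it.
- **The statistician is blinded.** This limits steering towards a favoured arm. It does not decide which covariates enter or which estimate is primary, and it does not recover precision.
- **Cancer type is not shown to be prognostic for EQ-5D.** Correct; including it is a judgement with a small cost.

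Three stronger readings are tempting, and the document does not support them. A reader might infer that the rule itself inflates type I error; followed strictly it does not (3.6% to 4.6% in step 4), and only picking the better result raises it, to 6.0% to 6.7%. A reader might infer that the regression would treat the three visits as independent rows; section 3.6.2 does not say so, and one row per patient or one regression per visit fits the wording equally well. A reader might infer that the therapy item is a post-randomisation covariate. It sits in a profile taken at the initial visit and may mean planned therapy, and nothing says that it would be adjusted for. What remains is a wording conflict with section 3.1.

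**Conclusion.** The point holds as a criticism of a stated rule. It is not a detail left to an analysis plan, because a plan that only filled in details would inherit the trigger. The rule chooses covariates by chance, fixes no prognostic covariate in advance, and leaves the primary estimate open between two analyses.

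The loss that can be shown from the protocol's own inputs is a variance factor of 0.40 instead of 0.31, or about 52% power instead of 63% at 40 per arm. This rests on equal correlation of 0.7 between all visits and on an effect averaged over follow-up. The trigger frequency of roughly 40% to 76% rests on the assumed 5% criterion, on independence, and on how the items are counted and tested. The simulation supports the direction of the loss, but its size depends on the assumed effect and R². The trial remains valid; the change should be made but is not critical.

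**What to change.** In section 3.6.2:
1. Delete the imbalance trigger.
2. Include baseline EQ-5D as a pre-specified covariate in the primary repeated-measures analysis, whatever the observed balance.
3. Name that analysis as the primary one.
4. Optionally add cancer type, with small types grouped, as a second pre-specified covariate.
5. Label any other adjustment as a sensitivity analysis.

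In section 3.4, reconcile the therapy item with the entry condition in section 3.1 by stating what is recorded at the initial visit. Treatment actually received after randomisation should not be used as a covariate.

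The cost is analysis wording, plus a few degrees of freedom if cancer type is added. Baseline EQ-5D and cancer type are already collected, so no further data or patients are needed.
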